## Abstract

**Background:**

Substance use disorder (SUD) involves excessive substance consumption and persistent reward-seeking behaviors, leading to serious physical, cognitive, and social consequences. This disorder is a global health crisis tied to increased mortality, unemployment, and reduced quality of life. Altered brain connectivity, circadian rhythms, and dopaminergic pathways contribute to sleep disorders, anxiety, and stress, which worsen SUD severity and relapse. Factors like trauma and socioeconomic disadvantages heighten risk. Digital health technologies, including wearables and machine learning, show promise for diagnosis, monitoring, and intervention, from relapse prediction to early detection of comorbidities. With high relapse rates and younger patient cases, these innovations could enhance the treatment outcomes of SUD.

**Objective:**

The objective of this study is to develop and validate a predictive model with machine learning for the duration of therapy and the rehabilitation or relapse in patients with SUD, using digital physiological measurements, psychological profiles, automatic facial emotion recognition, and the emotional state during craving.

**Methods:**

The study will be conducted with adult male patients with SUD at a rehabilitation center and control volunteers. Participants will undergo a self-reported demographic and psychological assessment, a clinician-administered craving and emotional reaction test, and will also be monitored using a smartwatch. SUD participants will be monitored for a total of 18 months (6 months during rehabilitation, an additional 12 months post discharge), and control participants for a total of 6 months. All participants will be reassessed at the sixth month of monitoring. The collected data will then be used to train models with a neural network, which will then be validated against other models and compared with other algorithms. Demographic, psychological, digital biomarkers, and craving profiles will be created, correlations will be analyzed, and they will be compared with controls to generate a digital phenotype of SUD. When the model achieves adequate validity (area under the curve of ≥0.80), a graphic user interface will then be designed for clinical use.

**Results:**

The study is supported by the Program for the Improvement of Working Conditions for Members of the SNII and SNCA (PROSNII U006EST), and APPAC-VII-CUCS-2025 for Article Publication Fees, from the University of Guadalajara. The research protocol was approved by the University of Guadalajara (reference CI-01225) in January 2025. Recruitment of patients with SUD and control participants will take place from January 2025 through January 2027.

**Conclusions:**

As shown in recent studies, accessible and affordable wearables, like commercial smartwatches, combined with psychological, demographic, and emotional state data, used with a machine learning predictive model, may be able to be used as tools to enhance SUD rehabilitation and prevent relapse.

**International Registered Report Identifier (IRRID):**

PRR1-10.2196/71374

## Introduction

Substance user disorder (SUD) is characterized by the excessive consumption of a substance, persevering and repetitive conducts of reward-seeking and reinforcing, regardless of the harmful physical, cognitive, behavioral, and social consequences. The disturbances created by SUD are related to alterations in brain connectivity, even after successful remission of substance use [1].

Worldwide, SUD is considered a multidimensional and critical health crisis phenomenon, connected with an increase in mortality, development of diseases, reduction of safety, increase in unemployment rates, and reduction of quality of life [2].

Research has suggested a link between the alteration of circadian rhythms and SUD in its earlier stages, that in time, due to the alteration of dopaminergic and glutamatergic pathways [3], results in sleep disorders. The development of these has been found to be a pivotal factor in the progression, severity, and relapse of SUD. These findings confirm a bidirectional relationship between SUD and sleep disorders [4-6].

Increased levels of anxiety and stress have also been associated with SUD, specifically in the abstinence and craving stages of the addiction cycle [7-12]. Anxiety and stress have also been related to an increase in heart rate, sweating, oxygenation levels, and atypical patterns of physical activity, all of which have been found in SUD [13-17].

In addition to physiological biomarkers, psychological evaluation has identified critical changes in executive function, decreased emotional regulation, and heightened levels of anxiety and depression [18-22]. Furthermore, environmental factors have been recognized to increase the risk of developing this disorder, like adverse experiences during childhood, violent or traumatic events, and disadvantageous economic conditions [23-29].

The first studies using digital technologies in mental health disorders were done on patients with major depressive disorder (MDD) through ecological moment assessment questionnaires through mobile devices, increasing a better treatment adherence [30-33]. After this study, various researches have been carried out, using varying methodologies and with objectives going from early diagnosis to prognosis of various complex pathologies, such as Alzheimer disease and major neurocognitive disorders some of the areas, where wearables and virtual reality have been used, allowing to observe cognitive decline and behavioral patterns [34-39].

Machine learning (ML) has also been used as a tool for the diagnosis of anxiety disorders with the use of speaking patterns, gaming activities, and self-reports [40-49]. It has also allowed researchers to measure the severity and variability of that disorder in varying environments through wearables, allowing remote intervention and through simulations [30,48,50-52]. It has also been used in predictive models for early depression diagnosis through smartphone use, severity, and progression through physical activity, sleep, and social interaction data [53-61]. In addition, ML models (MLM) have been trained to detect relapse in MDD and risk of suicide [62-64]. Similarly, it has been used to predict the start of a psychotic episode 5 days before it by using patterns of movement and sleep disturbance [63,65].

With a 60% relapse rate, an average of 5 recovery attempts required for full remission, and a growing number of new patients with SUD presenting at younger ages [2], this disorder represents a significant opportunity for digital health technologies. These tools, often used in managing cognitive and mood disorders commonly comorbid with SUD, have the potential to enhance treatment effectiveness and reduce relapse rates.

This study aims to integrate physiological, behavioral, and psychological data through digital technologies to develop comprehensive digital profiles of individuals with SUD. These profiles will be analyzed using ML tools to identify clinically relevant patterns. The resulting models are intended to serve as complementary tools in clinical practice, supporting treatment decisions, improving prognostic accuracy, and facilitating the monitoring of patients in remission.

## Methods

### Goal and Objectives

The purpose of this study is to develop and validate a predictive model of substance use relapse or rehabilitation with ML in patients with SUD. This will be through using digital physiological measurements (digital biomarkers), demographic and psychological profiles, automatic facial emotion recognition, and the emotional state during craving (ESDC).

### Study Design

This study adopts a prospective cohort design, using data collected from nontraditional experimental groups to develop a MLM aimed at predicting clinical outcomes in the rehabilitation or relapse of patients with substance use disorders. The model will rely on comparative analyses between groups, identifying patterns in physiological, psychological, and emotional reactivity data to enhance predictive accuracy.

No interventions will be implemented in either group as part of this study, ensuring that all collected data reflect naturalistic conditions and minimizes external influence on the observed outcomes.

### Participant Identification and Randomization

Participants in both groups will be randomly assigned a unique identification number, which will be used throughout the study to ensure anonymity and meet the inclusion criterion of randomization. Psychological assessments conducted at the rehabilitation center will be conducted through self-reported questionnaires, administered in a traditional pen-and-paper format, overseen by the institution’s psychologists, who will use only the assigned ID numbers during the digitization of all data. Control participants will complete all psychological tests in a self-reported computer-based format, using their ID numbers, which will be randomly assigned at the start of the monitoring period.

A secondary randomization process will be conducted to create k-clusters of data before training the ML algorithm. This step will also include the selection of test data for verification purposes, ensuring robust validation of the model.

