### Study Setting

Participants will be evaluated in person at the key time points outlined in Figure 1 by health care professionals trained in conducting clinical interviews, administering psychological tests, and assessing the ESDC. For patients with SUD, assessments will take place in a designated area within the rehabilitation treatment facility, ensuring both privacy and comfort. Control group participants will be assessed at the University Center of Health Sciences, University of Guadalajara, in Guadalajara, Mexico, by trained health professionals.

Passive monitoring of biological and digital measurements using a smart band will be conducted for at least 22 hours per day, allowing a threshold of 2.4 hours (20%) of lost daily data, 7 days a week. Participants will be required to wear the device during sleep. Participants’ physiological activity will be recorded during various activities and across diverse locations.

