### Instruments

The study instruments that will be used in this protocol to measure each assessment category referred to in the timeline (Figure 1), are presented in Table 1.

**Table 1 table1:** Study instruments.

Instrument	Period				
	Baseline	3 Months	6 Months	18 Months	Continuous
Wearable: Xiaomi Redmi Smart Band 8^a^	✓	✓	✓	✓ ^b^	✓
Demographic survey^c^	✓				
The Adverse Childhood Experiences Assessment (ACEs)^d^	✓				
The University of Rhode Island Change Assessment Scale (URICA)^d^	✓				
The Alcohol, Smoking and Substance Involvement Screening Test (ASSIST)^d^	✓				
The Beck Depression Inventory (BDI-II)^d^	✓				
The Beck Anxiety Inventory (BAI-II)^d^	✓				
The Pittsburgh Sleep Quality Index (PSQI)^d^	✓		✓	✓^b^	
Wechsler Adult Intelligence Scale IV (WAIS-IV): Digit Span and Letter-Number Sequencing subscales^d^	✓		✓		
Emotional Pictures Database (EmoMadrid)^e^		✓	✓		
Mannheimer Craving Scale (MaCS)^e^	✓	✓	✓		
Automatic facial emotion recognition software (FER)^e^		✓	✓		

^a^Digital measurement of biomarkers.

^b^Substance use disorder group only.

^c^Demographic assessment.

^d^Psychological assessments.

^e^Emotional state during craving assessment.

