### Demographic and Psychological Assessment

Demographic information, such as age, place of birth, education, occupation, civil status, household income, housing characteristics, as well as medical and family history, will be collected at baseline. A form will be filled in by the participant, assistance from the trained research staff will be provided if it is required.

The psychological tests will be administered at baseline within the first 15 days of participation. A battery of self-report questionnaires has been chosen to assess for a history of childhood trauma (Adverse Childhood Experiences Assessment [ACEs]) [68], the presence of depression or depressive symptoms (Beck Depression Inventory [BDI-II]) [69], anxiety and stress (Beck Anxiety Inventory [BAI-II]) [70], sleep disorders (Pittsburgh Sleep Quality Index [PSQI]) [71], and short-term memory (Wechsler Adult Intelligence Scale IV [WAIS-IV] subtests: Digit Span and Letter-Number Sequencing) [72]. Substance use–specific tests will aim to determine the type of substance, frequency and quantity of used drugs (Alcohol, Smoking and Substance Involvement Screening Test [ASSIST]) [73], level of substance craving (Mannheimer Craving Scale [MaCS]) [74], as well as the stage or frame of mind of the individual starting the therapeutic process (University of Rhode Island Change Assessment Scale [URICA]) [75].

To obtain a comparative measurement after treatment, depression, anxiety and stress, sleep disorders, short-term memory, stage of change and craving, will be reevaluated within fifteen days before the sixth month period of digital tracking ends (Figure 3).

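### Test format (paper for SUD patients, computer for controls) coincides with group, so SUD-control comparisons of psychological scores cannot be separated from a format effect

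*Protocol article*

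**What the plan says.** Under Participant Identification and Randomization, psychological assessment of patients at the rehabilitation center is by self-report and "administered in a traditional pen-and-paper format, overseen by the institution’s psychologists". The same paragraph then says of the other group: "Control participants will complete all psychological tests in a self-reported computer-based format, using their ID numbers".

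Table 1 (Instruments) marks the "Wechsler Adult Intelligence Scale IV (WAIS-IV): Digit Span and Letter-Number Sequencing subscales" as a psychological assessment, given at baseline and 6 months. Demographic and Psychological Assessment opens its list of tests with "A battery of self-report questionnaires has been chosen to assess for a history of childhood trauma" and ends the same sentence with these two subtests, as the measure of short-term memory.

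Study Setting has participants evaluated in person "by health care professionals trained in conducting clinical interviews, administering psychological tests, and assessing the ESDC", and adds: "Control group participants will be assessed at the University Center of Health Sciences", again by trained health professionals.

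The between-group contrast has several uses. Study Design bases the model on comparisons between groups that include psychological data. Profiles (under Outcomes) makes the psychological profile one of four that are combined into the digital phenotype. Predictive Model makes separating healthy individuals from SUD patients an outcome, with AUC and F2 thresholds of 0.8. Limitations and Considerations mentions self-report bias and participants' knowledge of their status, but not test format.

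**The concern.** When every patient answers on paper and every control on a screen, a difference in scores may come from the disorder, from the format, or from both. The data contain no patient tested on a computer and no control tested on paper, so nothing in them can apportion the difference. This is fixed when the data are collected, and a later analysis plan cannot repair it.

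At stake are the comparisons that set patients against controls. A format effect could create a difference in scales such as ACEs, BDI-II, BAI-II or PSQI, or hide a real one. In the classifier it would count as discrimination.

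The WAIS-IV subtests raise a separate question. The article uses them to measure memory, yet lists them in a self-report battery, and the literal control wording puts them in the self-reported computer format. It does not say plainly who gives them in each group.

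**Working it through.** The plan states no figure on this point, so there is none to reproduce.

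**1. Can group and format be separated?** Code group as 1 for SUD and 0 for control, and format as 0 for paper and 1 for computer. Under the stated procedure, format = 1 − group for every participant. The correlation is −1, and the matrix of intercept, group and format has rank 2 for 3 columns. A model with both terms cannot be estimated at any sample size.

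**2. Where does this matter?** Output sets five labels: timely or late rehabilitation, and early relapse, late relapse or one-year maintenance. All describe SUD patients, who share one format, so the problem does not reach those predictions. It reaches the profile comparison, the phenotype and the healthy-versus-SUD classifier.

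**3. How large could it be?** The format shift *m*, in SD units, is an assumption; the documents give none. Other inputs: zero true difference, normal scores with equal SD, and 25 per group (the minimum under Sample Size).

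- Single-scale AUC = Φ(m/√2).
- Two-sided 5% t test: 48 df, noncentrality m/√(2/25) = 3.536 m.

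| Assumed shift (SD) | Noncentrality | Single-scale AUC | Chance of p<0.05 |
|---|---|---|---|
| 0.2 | 0.71 | 0.56 | 11% |
| 0.3 | 1.06 | 0.58 | 18% |
| 0.5 | 1.77 | 0.64 | 41% |

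The nominal chance is 5%. The group mean difference is biased by *m* itself.

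**4. Several scales together.** For k independent scales all shifted by *m*, combined AUC = Φ(m√k/√2). With k = 6, shifts of 0.2, 0.3 and 0.5 SD give 0.64, 0.70 and 0.81. Independence makes these upper-end values: positively correlated scales shifted in the same direction would give less.

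**5. Administration and supervision.** Participant Identification and Randomization names overseers for patients and none for controls, but does not say that controls are unsupervised. Study Setting has controls assessed by trained professionals. A computer form filled in at a staffed visit fits both. The paper-versus-computer difference is therefore firm and the supervision difference is not.

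**The case against.** The strongest reply is that the study's main aim is prognosis within SUD patients, where format does not vary. This stands, and it limits the point to the SUD-control comparisons. A reader might infer that the relapse model is confounded as well, or that it would fail when used at the center. The labels under Output do not support that.

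A reader might also infer that patients are supervised and controls are not, or that Study Setting contradicts the computer format. Neither follows, because a computer form at a staffed visit satisfies both sections. Nor do the documents show that the WAIS-IV scores are invalid in either group. The battery sentence may be loosely worded, the patient text speaks only of questionnaires, and the battery flowchart is not shown. What stands is that the sections need reconciling.

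The size is assumed throughout. At 0.2 to 0.3 SD a single scale stays far below the 0.80 threshold, and Statistical Analysis frames the group tests as descriptive. Controls must have no SUD history and no current substance use, so a substance-use scale such as ASSIST should separate the groups by selection, and a modest format shift might add little to the classifier. It would be tempting to say that the classifier could reach its AUC threshold on format alone. That needs 0.5 SD on each of six independent scales, and nothing in the documents makes that likely.

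None of this removes the complete overlap of format and group, and the article plans no equivalence check.

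**Conclusion.** The point holds for the SUD-control comparisons of psychological scores, the digital phenotype and the healthy-versus-SUD classifier. It does not hold for therapy duration or relapse. That format and group cannot be separated follows from the stated procedure and needs no assumption. The size does: for shifts of 0.2 to 0.5 SD and no true difference, single-scale AUC would be 0.56 to 0.64, with a p<0.05 in about 11% to 41% of studies at 25 per group. The direction of any real effect is unknown. How the WAIS-IV subtests are given, and how controls are supervised, is unclear in the text and needs clarifying; neither is a demonstrated error. The change should be made while recruitment is open, but the main objective does not depend on it.

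**What to change.** **From now on**
- Use one format for all self-report scales in both groups, for example the center's paper forms for new controls too, completed at the in-person visits in Study Setting.
- State that trained staff administer the two WAIS-IV subtests in the same way in both groups.
- Reconcile Participant Identification and Randomization, Study Setting, and Demographic and Psychological Assessment on these points, including how controls are supervised.

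**For the 35 already enrolled (18 SUD, 17 controls, as of June 2025)**
- Record the format of each score and keep the baseline data.
- Report the SUD-control comparison and the classifier with a sensitivity analysis that leaves out format-mismatched scores.
- If new controls use paper, compare early with late controls as a rough check of the format effect. At the minimum of 25 controls, if the change came straight after the first 17, only 25 − 17 = 8 would be late. The standard error would be √(1/17 + 1/8) = 0.43 SD, so the check could not exclude a moderate shift. It would also mix format with time of enrolment.

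**What to avoid.** Do not replace baseline comparisons with month-6 values. ACEs is measured only at baseline. BDI-II and BAI-II are baseline-only in Table 1, although the assessment section retests depression and anxiety. That section also describes the retest as following treatment, so the substitution would change the question.

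**Cost.** Digitizing paper forms for controls, some staff time per control visit, and mixed formats among controls that must be flagged. Trained staff already see controls in person.

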### Blinding

Due to the nature of this study, neither the participants nor the first group of research staff will be blinded to group assignments. However, the group allocation of participant ID clusters will remain concealed from the second group of researchers. This second group will be responsible for data management, training the ML algorithm with the predictive model, and conducting validation, verification, and testing of the highest-performing models.

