### Timeline

This study will include 2 types of observations: continuous passive monitoring and active surveys conducted at specific time points. Passive monitoring will occur continuously for 6 months in both groups, followed by an additional year for participants with SUD after their discharge from the treatment facility. Active surveys will be conducted at three time points: (1) baseline session or baseline, (2) 3 months after baseline, and (3) 6 months after baseline.

For digital monitoring purposes, smart bands provided to participants will be synchronized with a smartphone at the baseline session. Psychological assessment will be conducted within the first 15 days after baseline. Retesting will take place during the 15 days prior to the 6 months after baseline. Emotional reactions to cravings will be assessed at two points: (1) 3 months after baseline and (2) at 6 months after baseline (Figures 1A-1F).

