### Data Exclusion

Missing data will be addressed through imputation. If more than 20% of daily data samples are missing, they will be excluded. For missing data below this threshold, linear interpolation and neighbor mean imputation (k-nearest neighbor) will be applied during preprocessing using MATLAB.

The quality of data collected from the smart band will be assessed by correlating heart rate at randomly selected timestamps with oxygen saturation, activity levels, self-reported exercise, and sleep type during sleep hours. If atypical correlations are identified, 10 data points before and after the anomaly, along with 5 additional randomly chosen timestamps, will be reviewed. A day with more than 20% of faulty measurements will be excluded from the dataset.

Data will also be excluded in cases of device misuse, such as exchanging the device with other participants or nonparticipants, switching the wearing side without prior notice, or removing the device for more than 5 hours without informing the research team.

If the total sum of missing and excluded data exceeds 20% of the 6-month period, the participant's data will be removed from the study. Finally, for SUD participants, any measurements obtained during periods of substance use will be excluded, and their participation in the study will be terminated.

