**Figure 5 figure5:**
[figure not shown]
Model’s possible outputs. These categories will be used as output labels of the predictive model and will allow the evaluation of the patterns detected from the input.

For the duration of the therapeutic process, the following labels will be used:

Timely rehabilitation: patients with SUD who complete the rehabilitation protocol within 7 months.Late rehabilitation: patients with SUD who complete the protocol in 7 months or longer.

Regarding relapse latency, the labels will include the following:

Early relapse: substance use occurring within the first 6 months post discharge.Late relapse: substance use occurring after 6 months but before the completion of 18 months post discharge.One-year maintenance: patients who have abstained from substance use at the end of the 18-month postrecovery period.

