### Validation and Verification

All models and algorithms will undergo validation, verification, and testing using MATLAB’s tools for model evaluation and hyperparameter optimization. These processes will assess precision, performance, and recall metrics. Optimal model performance will be defined by achieving an area under the curve (AUC) of ≥0.80 and F2 score of ≥0.8.

The output categories will serve as benchmarks to evaluate the validity, reliability, and precision of the models. The validation dataset will be used to perform initial comparisons both within individual models of each algorithm and across different algorithms, replicating models with distinct architectures to refine performance.

For model verification, the test dataset will be used to determine final AUC and F2 scores. This final evaluation will confirm the models’ effectiveness as ML tools for predicting rehabilitation outcomes and informing clinical decision-making.

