#### Predictive Model

A predictive model will be developed to distinguish between healthy individuals and patients with SUD. In addition, the model will predict the duration of a rehabilitation therapeutic program and the length of sobriety adherence for individuals rehabilitated using the center’s methodology. A minimum performance threshold of AUC≥0.8 and F2≥0.8 has been established to evaluate the model as fully functional.

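### The stated concealment of group from the modelling team cannot hold through training and testing, because group is a training target and the data reveal it

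*Protocol article*

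**What the plan says.** The Blinding section describes two teams. For the first, and for participants, there is no blind: "neither the participants nor the first group of research staff will be blinded to group assignments". For the second it promises that "the group allocation of participant ID clusters will remain concealed from the second group of researchers". It then lists that team's work: "This second group will be responsible for data management, training the ML algorithm with the predictive model, and conducting validation, verification, and testing".

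The models to be built are described elsewhere. Under Predictive Model: "A predictive model will be developed to distinguish between healthy individuals and patients with SUD". The same section adds prediction of therapy duration and of how long sobriety lasts. The labels for these, listed with Figure 5, include "Timely rehabilitation: patients with SUD who complete the rehabilitation protocol within 7 months", and the three relapse categories are counted from discharge or recovery. Under Validation and Verification, "The output categories will serve as benchmarks to evaluate the validity, reliability, and precision of the models".

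On follow-up, the Timeline gives both groups six months of passive monitoring, "followed by an additional year for participants with SUD after their discharge from the treatment facility". Limitations and Considerations acknowledges a possible early inference of group by staff, and attributes it to clustering the data by group before final testing.

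**The concern.** A blind stated in a protocol tells readers that certain decisions were made without knowledge of the thing concealed. Here the team said to be blind to group is the one that needs group to do its work. If the statement stays, readers will credit data management, model selection and final testing with a safeguard that the design cannot supply.

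Two kinds of decision are at stake. One is the part of band-data cleaning that rests on judgment: what counts as an atypical correlation or a faulty measurement. The Data Exclusion section starts a review from such a judgment ("If atypical correlations are identified, 10 data points before and after the anomaly"), and the result can remove days and, cumulatively, a participant. The other is the choice among models before final scoring. Both feed the AUC and F2 thresholds of 0.80, and the Abstract makes reaching the AUC threshold the condition for building the clinical interface. The planned minimum is 25 per group, so one excluded participant is 1/25 = 4% of a group.

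**Working it through.** The document gives no figure to reproduce. The check sets the stated blind beside the tasks, labels and data given to the same team.

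**1. Tasks.** A supervised healthy-versus-SUD classifier cannot be trained without each training participant's class, and that class is group. F2 weights recall of a positive class, so it cannot be scored until someone has said which class is positive.

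**2. Labels.** The two duration labels (Figure 5) are defined for patients with SUD. The three relapse labels need a discharge or recovery date, which controls do not have. Any participant carrying one of the five labels is therefore an SUD participant.

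**3. Would neutral codes (A and B) help?** They would hide the names of the groups, but the data would still show which is which:
- *Monitoring length* (Abstract, Timeline): SUD 6 + 12 = 18 months, controls 6 months. The difference is 18 − 6 = 12 months, so 12/18, or two thirds, of planned SUD monitoring has no counterpart in controls. Any record running past month 6 is an SUD record.
- *Assessments* (Table 1): the 18-month PSQI and wearable entries are marked for the SUD group only.
- *Instrument content* (Control Participants; Demographic and Psychological Assessment): controls must be free of SUD history and current use, while ASSIST records which drugs are used, how often and how much.
- *Processing* (Limitations and Considerations): activity is coded from app self-report in controls, with the facility timetable also used for SUD patients. Whoever codes it must know which applies.
- *Exclusion* (Data Exclusion): one rule, on measurements taken during substance use, names SUD participants.

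Any one of the first three is enough to identify group for most participants.

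**4. The document's own caveat.** Limitations and Considerations treats unmasking as something that might happen through clustering. Steps 1 to 3 show that it follows from the labels and the data whether or not they are clustered. The mitigation offered there is adherence to general machine-learning guidelines, with no step specific to this problem.

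**5. Which results could be affected?** Knowing that a record is SUD says nothing about timely versus late rehabilitation, or early versus late relapse, within that group. The failed group blind therefore bears on the healthy-versus-SUD classifier. For the duration and relapse models the relevant knowledge is outcome, and the Blinding section does not promise to conceal that.

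**The case against.** **The plan never claims an outcome blind.** This stands. A reader might infer that a promise to hide relapse status has been broken. The Blinding section conceals group only, so no outcome blind exists to fail.

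**The test set is protected.** This stands in large part. A reader might infer repeated looks at test labels. Validation and Verification assigns comparisons within and across algorithms to the validation data and keeps the test data for final scores. What the article lacks is a stated separation of people: the team that tunes also tests.

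**Exclusions are mostly rule-based.** This largely stands. Data Exclusion fixes 20% limits for daily samples, faulty measurements and the six-month total, a five-hour limit on unannounced removal, and the number of points reviewed. What is atypical or faulty remains open. Exclusion decisions are not assigned explicitly to the second team, although data management is.

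**Timing limits outcome-aware cleaning.** This stands for early data. Digital Measurement of Biomarkers has data preprocessed and available within 48 hours of download, before most relapse labels could exist. Data Preprocessing describes further cleaning without a date, so the risk is reduced but not removed.

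**The problem is disclosed.** Only partly, as step 4 of the working shows.

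**The concealed clusters might mean data folds.** The preceding sentence in Blinding and the caveat in Limitations both speak of group assignments, so this reading is unlikely. If it is the intended one, the wording still needs changing.

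**Modellers need not be blind to group.** Agreed, and in that case the protocol should not say that they are.

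**Conclusion.** The concern holds as an internal contradiction: the concealment of group stated under Blinding is incompatible with the tasks, labels and data of the team it covers, and cannot last through training and testing. This rests on the document's own text and needs no numerical assumption. Brief masking during early preprocessing remains conceivable, and the random ID numbers still protect identity, so it would be too much to say that the arrangement protects nothing.

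The size of any bias in AUC or F2 cannot be derived from the documents. Upward is the probable direction if judgment-based exclusions or model choices are made with labels in view, but that is an expectation and not a result. A reader might infer that performance will be inflated or that outcome-aware exclusion is planned. The documents show only that neither is ruled out. The wording on group should be corrected. Safeguarding the outcome labels is a worthwhile, inexpensive addition.

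**What to change.** 1. Reword the Blinding section to say that the modelling team is not blind to group during training, and align Limitations and Considerations with it.
2. Complete and freeze the judgment-based band-data checks in Data Exclusion (atypical correlations, faulty measurements) for the whole monitoring period, before duration and relapse labels are linked. The unblinded first group applies the substance-use exclusion and the timetable-based activity coding, since both require knowledge of group.
3. Have the first group hold the test participants' duration and relapse labels and release them once, after the final model is locked.

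Step 2 does not make cleaning blind to group, because record length and activity coding still show it. Nor does it hide outcome fully: Withdrawal Criteria ends participation at relapse, so a retained SUD record that stops early in the post-discharge year may hint at it. Step 2 does fix the judgments before the labels are attached.

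The cost is protocol wording and the order of existing steps, using the two teams already in place. The downsides are a short delay before labels are linked and no re-tuning once the test labels are open. The Results section reports data at the labelling and preprocessing stage as of June 2025 and publication expected by summer 2028, so there is time to make the change.
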